### The ENABLE Cornerstone Intervention

Caregivers randomized to the intervention condition are paired with a specially trained lay navigator coach. The lay navigator coach’s roles are to (1) provide basic psychoeducation on relevant caregiving topics; (2) offer health coaching and problem-solving support for problems and self-care goals identified by caregivers; (3) perform caregiver distress screening and support; (4) bridge the communication gap between the healthcare team and the family and patient as needed; (5) provide families with the appropriate cancer-specific institutional, local, state, and national resources; (6) offer basic psychological and emotional support; and (7) serve as a continuity figure for the caregiver during the patient’s trajectory of serious illness, from diagnosis of advanced disease to bereavement.

After contacting the participant by phone, the coach and caregiver proceed with scheduling six weekly coaching sessions. Coaching sessions can be conducted in-person at a mutually agreed upon location (including the participant’s home) or over the phone. However, all sessions have been conducted over the phone since the emergence of COVID-19 in March 2020 to the date of this publication. Core coaching sessions cover specific caregiver topics identified from our formative evaluation study (Table 1) [28]. Sessions are designed to last approximately 20 min but may last up to 1 h if desired by the participant. The six sessions are followed by monthly follow-up calls that focus on monitoring caregivers’ distress (via distress screening), reinforcing content covered in core sessions, providing additional informational materials, and initiating referrals for additional support. For caregivers of patients who die, coaches conduct a bereavement call approximately 2 to 6 weeks after the person’s death to acknowledge and express sympathy for the caregiver’s loss and to provide and review additional bereavement materials and resources.

**Table 1 Tab1:** ENABLE cornerstone core sessions, monthly follow-up, and bereavement call

Core session	Objective	Content
Session 1: Caregiving story	Establish therapeutic alliance by exploring and validating the individual’s caregiving situation	- Supporting someone with cancer - National caregiving statistics and commonly experienced challenges - Understanding your caregiving experience, including biggest current and future concerns and what gives you strength -Orientation to and administration of caregiving distress thermometer
Session 2: Coping with stress	Introduce caregivers to the stress process model and discuss ways to cope with stress	- Distress screening - How stress works - Ways to cope with stress - Action plan for the coming week
Session 3: Getting help	Motivate effective social support through asking for and getting help	- Distress screening - Why some families do not ask for help - Getting help from family, friends, and community resources - 3 options for accomplishing caregiving tasks: doing it yourself, asking for volunteers (e.g., other family members and friends), and paying for help - How to decide what to take on yourself and when to ask others for help - Action plan for the coming week
Session 4: Improving your support skills	Enhance caregiving skills and organization	- Distress screening - Tips for organizing health information, managing medications, and tracking symptoms - Providing your loved one the “right” amount and type of support - Action plan for the coming week
Session 5: Taking care of yourself	Improve and reinforce self-care behaviors	- Distress screening - Maintaining health while under stress - Completing a self-care inventory and developing a personal health plan - Action plan for the coming week
Session 6: Decision-making and planning for the future	Help develop plans for the future to help mitigate future stressors and potential crises	- Distress screening - Partnering with patients to make decisions in serious illness - Making decisions about cancer treatment, advance care planning, and advance directives - Basic principles of communication when making decisions - Action plan for the coming month
Monthly follow-up (every 4 weeks)	Ensure continuity of care, conduct caregiver distress screening, and reinforce content covered in core sessions	- Distress screening - Additional informational materials and/or initiate referrals for additional support

Prior to the first core session, intervention group caregivers are mailed a study team-developed Project ENABLE Cornerstone Toolkit. This 3-ring, self-enclosed binder contains educational information pertaining to the six core sessions and serves as an all-in-one organizational binder for intervention materials and resources (i.e., business card holders; FCG tracking sheets for patient medications, tests, and procedures; and a calendar).

#### Conceptual basis of ENABLE Cornerstone

The ENABLE Cornerstone intervention is conceptually based on our team’s adapted version of Pearlin’s Stress-Health Process Model (Fig. 3) [29], which consists of three primary domains: the FCG, the caregiver and patient relationship, and the patient. Within these domains are specific key constructs, each preceded by a letter. In Fig. 4, definitions of these key constructs are shown on the left panel, while on the right panel, we link each Cornerstone session with constructs in the model they are designed to enhance. Cornerstone ultimately seeks to reduce stressors (B), enhance the caregiver’s capacity to appraise stressors (C, D), and change caregivers’ negative emotional and behavioral responses (E) by enhancing their coping skills (G). We believe this should subsequently decrease overall distress for the caregiver (F) and enhance their ability to provide high-quality social support to the patient (H). This would thereby optimize the patient’s quality of life (I) and their healthcare utilization (J).

**Fig. 3 Fig3:**
[figure not shown]
Adapted Pearlin’s Stress-Health Process Model of Family Caregiving

**Fig. 4 Fig4:**
[figure not shown]
Stress-Health Process Elements and Cornerstone Components Targeting those Elements

#### Discontinuation of study intervention

Participants may withdraw from the study or voluntarily stop intervention sessions at any time. Reasons for discontinuing the intervention are documented (e.g., too burdensome, too busy, patient too ill), though the participant is invited to continue with data collection. The PI can also discontinue a participant from the study for the following reasons: (1) significant study intervention non-adherence, (2) lost to follow-up, or (3) occurrence of an event, medical condition, or situation such that continued collection of study data would not be in the best interest of the participant.

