### Randomization and blinding

Randomization occurs at the level of the caregiver participant, with participating patients assigned to the same group as their caregiver. The randomization scheme is executed via REDCap (Research Electronic Data Capture) [37], a secure web-based software platform designed to support randomization and data capture for research studies. Participants are randomly assigned (1:1) using a computer-generated program overseen by the trial statistician. The randomization scheme is stratified by site (UAB and MCI) and blocked within strata (using random block lengths 4 and 10). After randomizing a FCG in REDCap and if selected for the Cornerstone program, the assigned lay navigator informs them by phone of their group assignment and introduces the intervention activities. If randomized to the usual care group, the program manager notifies FCGs by mail of their group assignment. All other members of the research team, including the principal investigator (PI) and all co-investigators, are blind to group assignment and participants are instructed to not discuss their assignment with study staff. The allocation sequence will remain concealed until the last participant completes 24-week data collection and the data have been checked for completeness and accuracy.

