### Usual care

Guided by NIH consensus panel recommendations [41], we determined that a usual care condition was the optimal comparator to best serve the aims of this trial. Usual care at both the UAB and MCI sites consists of resources focused primarily on the patient; no specific caregiver services exist to support their unique needs. A usual care comparison will test whether caregivers experiencing distress need more active support than what is currently offered by traditional services. Immediately after randomization, participants in both groups are mailed pamphlets outlining UAB and MCI resources for families. To further examine and describe usual care [42], we are collecting information from participants in both conditions on whether patients and/or FCGs on behalf of patients accessed UAB or MCI resources for families.

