10	Monthly follow-up, bereavement, and suicide protocol	Learn how to check in with family caregivers monthly, provide condolences and support after a patient’s death, and act if a family member or patient expresses a desire to harm themself or others.

Throughout the study, lay navigator coaches engage in weekly supervisory meetings with the PI (a board-certified palliative care advanced practice nurse [[name]]) and a nurse practitioner co-investigator ([name]) to review calls and sessions with all active intervention group participants, including adverse events. In addition, coaches have 24/7 access to the PI for any acute participant issues that arise.

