### Statistical analysis plan

An intention-to-treat (ITT) approach will be used for analyses of Aims 1 and 2. Primary data analysis will begin with baseline descriptive statistics for baseline caregiver and patient characteristics and outcomes. The balance between study groups will be examined with respect to baseline characteristics using effect sizes. Conceptually relevant baseline factors showing non-trivial imbalances between groups will be used as adjusting covariates in longitudinal comparisons using linear mixed-effect modeling. Distributional assumptions will be examined, and when appropriate, we will employ inferential and modeling procedures robust to distributional assumptions.

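### The PI may remove caregivers from the study for intervention non-adherence, which permits avoidable loss of outcomes in the Cornerstone arm only and undermines the intention-to-treat analysis

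*Protocol article*

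**What the plan says.** All references are to the Protocol article.

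- **Discontinuation of study intervention** first covers people who leave the study or stop sessions by choice. For those who stop the intervention, the reason is recorded, "though the participant is invited to continue with data collection". The next sentence gives the PI a separate power: "The PI can also discontinue a participant from the study for the following reasons: (1) significant study intervention non-adherence, (2) lost to follow-up". A third ground is an event, condition or "situation such that continued collection of study data would not be in the best interest of the participant".
- **Statistical analysis plan:** "An intention-to-treat (ITT) approach will be used for analyses of Aims 1 and 2". Imbalanced baseline factors serve as "adjusting covariates in longitudinal comparisons using linear mixed-effect modeling".
- **Usual care:** both groups are mailed resource pamphlets; beyond that, "no specific caregiver services exist to support their unique needs".
- **Randomization and blinding:** research team members other than those who notify caregivers of their group, "including the principal investigator (PI) and all co-investigators, are blind to group assignment".
- **Interventionist training and oversight:** coaches meet the PI weekly "to review calls and sessions with all active intervention group participants, including adverse events".

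**The concern.** The section treats two similar caregivers differently. One who says she is stopping the sessions is asked to go on returning questionnaires. One who simply does not take part can be taken off the study by the PI. In both cases coaching has ceased; only in the second may the outcome be lost, and by decision.

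That loss can fall in one arm only, and it depends on behaviour after randomisation that may be related to distress, the primary outcome. The article's own examples of why caregivers discontinue (burden, lack of time, a sicker patient) make such a link plausible. An intention-to-treat comparison needs outcomes on everyone randomised, whatever coaching they took up. A rule that creates missing outcomes because coaching was not taken up works against it, and an analysis plan cannot restore data that were never collected.

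**Working it through.** **1. Does removal mean that data collection ends?** The section separates leaving the study from stopping sessions, and the PI's power is worded as removal from the study. The third ground, in the same sentence, is framed in terms of continued data collection. The natural reading is that all three grounds end outcome collection. Nothing in the article says that people removed for non-adherence are still assessed.

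**2. In which arm can each ground arise?** Loss to follow-up and the participant's best interest can arise in either arm. Non-adherence can arise only in Cornerstone, because usual care has no study intervention to adhere to. Applying that ground reveals the arm, and the weekly review gives the PI the information needed to apply it. This cannot be squared with a blind PI.

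**3. When would it act?** Core sessions are weekly for six weeks and the first follow-up is at 12 weeks. A caregiver judged non-adherent on the core sessions could therefore be removed with baseline data only.

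**4. The plan's own figure.** The sample size supplies the variance used below. With d = .37, α = .025 two-sided (the sidedness is not stated), 80% power, ρ = .5 and variance factor (1 + ρ)/2 = .75 for the mean of two follow-ups:

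n = 2 × (2.2414 + 0.8416)² × .75 / .37² = 104.1 per group, or 105 rounded up.

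The article gives 103; power at 103 is 79.5%. The figure reproduces closely. It neither supports nor weakens the point.

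**5. Illustration of size.** Neither the share removed nor the prognosis of those removed is in the documents, so both are assumed. Let p be the share of the Cornerstone arm removed with no follow-up, and g the gap in follow-up HADS (removed minus retained) that would have been seen. The full-arm mean is (1 − p) × retained mean + p × removed mean, so using only the retained shifts the arm mean, and hence the difference, by p × g. Type I error assumes no true effect, SD 3.9, factor .75, and 120 per arm before removal:

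SE = 3.9 × √.75 × √(1/120 + 1/(120(1 − p)))

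| p | Shift at g = 1 | Shift at g = 2 | Type I error, g = 0 | g = 1 | g = 2 |
|---|---|---|---|---|---|
| 5% | 0.05 | 0.10 | .025 | .026 | .029 |
| 10% | 0.10 | 0.20 | .025 | .029 | .040 |
| 20% | 0.20 | 0.40 | .025 | .039 | .085 |

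Against the 1.5-point MCID, the largest shift is 0.4/1.5 = 27%. If g is negative (removed caregivers were coping better), the shifts have the same size against Cornerstone, and the two-sided error rates are unchanged.

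**6. What the mixed model recovers.** Take p = 20%, a follow-up gap of 2 points, the same gap at baseline and ρ = .5 with equal variances. The baseline value then predicts .5 × 2 = 1 point of the gap. The remaining shift is .20 × (2 − 1) = 0.2 points instead of 0.4. If the removed caregivers did not differ at baseline, nothing is recovered.

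**The case against.** A reader might infer that the rule breaks intention-to-treat, or turns the trial into a per-protocol comparison. The documents do not support that. Nothing says removed caregivers leave the analysis set or that their earlier data are discarded. Randomisation follows receipt of the baseline survey, so each has at least a baseline value and can be analysed as randomised in the mixed model. The damage is arm-specific missing follow-up, handled under an assumption that cannot be tested.

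A reader might also infer that the bias favours Cornerstone. That requires removed caregivers to be those who would have scored worse. Some may skip coaching because they are coping well, and the sign then reverses. With no gap there is no shift under a true null.

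The rule is also permissive. Caregivers who stop of their own accord because they are overburdened fall under the invitation to continue data collection. The PI's power matters only for those who are non-adherent, have not formally stopped, are removed, and would otherwise have returned questionnaires. That group may be small, and the article reports high data-collection completion in the pilot. The section heading refers to the intervention, so looser drafting than intended is possible. How non-adherence is defined may stand in the full protocol, and its absence from an article is no fault.

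All of this limits the size of the problem. It does not remove the stated power, its one-arm reach or its conflict with the preceding sentence. Whether the recruitment target allows enough for dropout is a separate question on which nothing here depends.

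**Conclusion.** The point holds in this form: the article permits avoidable loss of 12- and 24-week outcomes, in the Cornerstone arm only, on a ground that may be related to distress and that a blind PI could not apply. This undermines the intention-to-treat analysis of Aims 1 and 2 without abolishing it.

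The direction and size of any bias are unknown. The range of 0 to 0.4 HADS points, in either direction, rests wholly on the assumed 5-20% removed and 0-2 point gap, and on no recovery from earlier HADS values. At the low end it is negligible. At the high end it is about a quarter of the MCID, with type I error of .085 instead of .025. The case for correction rests less on those figures than on the fact that the missingness is created by a rule and is cheap to prevent.

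**What to change.** Reconcile the two sentences under Discontinuation of study intervention by stating that intervention non-adherence does not end outcome data collection. Such caregivers, and their patients where participating, stay on the scheduled mailings and are analysed as randomised. Record loss to follow-up as an observed status, not as a decision of the PI. Leave the third ground unchanged. This says nothing about when coaching should end; it only separates that decision from outcome collection. It also stops the PI's knowledge of the arm from determining, by this route, who has outcomes. The wider conflict between the blinding statement and the weekly supervisory review still has to be reconciled.

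The cost is a protocol amendment (two IRBs approved the protocol, and recruitment began in January 2021) plus questionnaires and incentives for those retained. At the stated rates the incentives are $50 + $60 = $110 per participant through 24 weeks. On the assumed 5-20% of 147, that is about 7 to 29 caregivers, or $770 to $3,190, and up to twice that if every patient also takes part. Each later 12-week time point adds $30 per participant. The change works forward only: outcomes already lost under the present rule cannot be recovered, so any removals made on this ground should be counted and reported.

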### Usual care

Guided by NIH consensus panel recommendations [41], we determined that a usual care condition was the optimal comparator to best serve the aims of this trial. Usual care at both the UAB and MCI sites consists of resources focused primarily on the patient; no specific caregiver services exist to support their unique needs. A usual care comparison will test whether caregivers experiencing distress need more active support than what is currently offered by traditional services. Immediately after randomization, participants in both groups are mailed pamphlets outlining UAB and MCI resources for families. To further examine and describe usual care [42], we are collecting information from participants in both conditions on whether patients and/or FCGs on behalf of patients accessed UAB or MCI resources for families.

### Interventionist training and oversight

To facilitate future replication and dissemination of ENABLE Cornerstone, should it demonstrate efficacy, our team has developed a structured orientation and training curriculum to prepare lay navigator coaches, based on our team’s lay navigator expertise [43–45] and training approaches from our prior trials [21, 22, 24, 46]. The training program (see Table 2) consists of 10 modules (~70 h total) housed on a web-based education platform called Canvas. Each module includes independent readings, videos demonstrating coaching techniques (e.g., active listening, single- and double-sided reflections, action planning), for all study protocols, procedures, and scripts, example session recordings, and one-on-one role-playing practice for each of the six sessions with a standardized caregiver.

**Table 2 Tab2:** Description of project cornerstone RCT coach training

Module	Title	Description
1	Before you get started	Access and orientation to study files and tracking.
2	Fundamentals of supportive care coaching	Cover fundamentals of oncology navigation, health coaching, family caregiving, and palliative care in oncology.
3	What is this study about?	Review background on Project Cornerstone and protocols of the current trial.
4	Cornerstone Session 1: Caregiving story	Establish rapport with caregivers, orient them to the Toolkit, ask them about their day-to-day lives, and administer distress screening.
5	Cornerstone Session 2: Coping with stress	Educate caregivers about the stress process model and how to cope with stress.
6	Cornerstone Session 3: Getting help	Review why caregivers do not ask for help and how to accomplish caregiving tasks by leveraging outside help.
7	Cornerstone Session 4: Caregiving skills	Review tips for organizing health information and medications and how to track symptoms; provide guidance on how to communicate with care recipients about the type and amount of support they desire.
8	Cornerstone Session 5: Self-care	Review and discuss self-care and facilitate a comprehensive self-care assessment with family member participants.
9	Cornerstone Session 6: Decision-making and advance care planning	Discuss decision-making in serious illness and the role of family members.
10	Monthly follow-up, bereavement, and suicide protocol	Learn how to check in with family caregivers monthly, provide condolences and support after a patient’s death, and act if a family member or patient expresses a desire to harm themself or others.

Throughout the study, lay navigator coaches engage in weekly supervisory meetings with the PI (a board-certified palliative care advanced practice nurse [[name]]) and a nurse practitioner co-investigator ([name]) to review calls and sessions with all active intervention group participants, including adverse events. In addition, coaches have 24/7 access to the PI for any acute participant issues that arise.

### Treatment fidelity monitoring

Four strategies (consistent with NIH and the Template for Intervention Description and Replication [TIDieR] guidelines) [47, 48] are being employed to ensure intervention fidelity. First, as described above, there is structured and standardized training for all interventionists. Second, interventionists use guiding scripts for each of the core sessions and monthly follow-up calls. Third, charting templates are used by interventionists for each intervention contact to further ensure that all materials are covered. Finally, all core sessions are audio recorded by coaches and 25% are randomly selected on a quarterly basis for treatment fidelity monitoring by a study team member using a fidelity checklist. If ratings for a coach fall below 80% adherence, retraining in underperforming areas will be overseen by the PI.

